## Abstract

**Background:**

Turner syndrome (TS) is a chromosomal disorder caused by complete or partial loss of one X chromosome, resulting in a high risk of premature ovarian insufficiency (POI) and infertility. While the underlying mechanisms are not fully understood, oocyte loss is known to begin in fetal life and continue throughout childhood, often leading to ovarian failure before the onset of puberty. Ovarian tissue cryopreservation (OTC) offers a potential method to preserve fertility in girls with TS, but the procedure remains experimental in this group. To date, only three cases of autotransplantation have been reported, and no live births have occurred in women with TS. Moreover, predictors of residual ovarian function and eligibility for OTC are poorly defined, and the long-term effects of unilateral oophorectomy in girls with already limited ovarian reserve are unknown.

**Objective:**

To investigate long-term reproductive outcomes following OTC in girls with TS.

**Methods:**

The Danish Turner Syndrome Cryopreservation Study is a nationwide, prospective cohort study with long-term follow-up, combining observational and interventional elements. Girls with TS aged 2–17 years are invited to participate. As ovarian reserve is depleted before adulthood in most girls with TS, all participants undergo ovarian function assessment to evaluate the likelihood of remaining viable follicles. If follicles are deemed present, unilateral OTC may be offered. The primary outcome is the number of pregnancies, miscarriages, and live births following autotransplantation of cryopreserved and thawed ovarian tissue in adulthood. Secondary objectives include identifying early predictors of POI, assessing the impact of oophorectomy on ovarian function and pubertal progression, and exploring molecular mechanisms of ovarian dysgenesis through genetic and epigenetic analyses of ovarian and peripheral tissues. Recruitment began in January 2024 and is ongoing at three university hospitals across Denmark. Follow-up is expected to continue until 2050.

**Conclusion:**

This study addresses a critical gap in fertility preservation for girls with TS by evaluating the feasibility and long-term outcomes of OTC. The findings will improve understanding of POI progression, refine selection criteria for OTC, and support evidence-based counselling for girls with TS and their families.

**Trial registration:**

ClinicalTrials.gov, NCT05740579. Registered 13 February 2023. https//clinicaltrials.gov/study/NCT05740579.

## Background

Turner syndrome (TS) is a chromosomal disorder affecting approximately 1 in 2000 live born females (ORPHA:881) [1]. It is caused by the complete or partial loss of one X chromosome, either in all cells or in a mosaic form with two or more different cell lines [2]. A hallmark feature of TS is premature ovarian insufficiency (POI), which is present in up to 95% of women with TS [3]. The exact mechanisms leading to ovarian failure in TS are not fully understood. However, an accelerated loss of germ cells begins in early fetal development [4–6], appears to continue throughout fetal life, and progresses rapidly during early childhood [7]. The underlying mechanisms involve increased apoptosis of oocytes and impaired formation of primordial follicles, resulting in compromised folliculogenesis during fetal life [5]. The accelerated loss of germ cells often leads to ovarian failure before the onset of puberty. However, a subset of patients retain sufficient ovarian function to undergo spontaneous pubertal development. More than one third of girls with TS develop signs of puberty, although only 15–35% experience spontaneous menarche [8–10]. Consequently, unassisted pregnancies are rare in women with TS, occurring in only 5–7% [11]. Notably, pubertal development, ovarian function, and fertility potential are highly dependent on karyotype. Girls with 45,X/46,XX mosaicism have the highest chance of retaining ovarian function, whereas girls with a 45,X karyotype are often born with fibrous streak gonads [12–14].

While TS is associated with multiple health challenges, infertility remains one of the most emotionally distressing, with the inability to have a genetically related child representing a major source of grief [15]. Ovarian tissue cryopreservation (OTC) presents a unique opportunity to preserve fertility in girls with TS before the complete depletion of germ cells. In contrast to oocyte vitrification, which requires post-pubertal maturation, OTC can be performed regardless of pubertal status, making it feasible even in infancy and early childhood. While OTC has proven successful in pediatric cancer patients treated with gonadotoxic therapy [16], its use in girls with TS remains experimental. Only a few TS cohorts have undergone OTC in Sweden [14, 17], the Netherlands [18], Denmark, the United Kingdom, and Australia [19]. Reports of subsequent autotransplantation are extremely limited, with only three documented cases in females with TS [17, 20]. Of these, only one reported a subsequent pregnancy, which unfortunately ended in an early miscarriage.

The Danish Turner syndrome Cryopreservation Study is a prospective cohort study designed to evaluate the long-term reproductive outcomes following OTC in childhood and subsequent autotransplantation in adulthood in women with TS. The study will also explore the natural history of TS, with particular focus on the progression of premature ovarian insufficiency (POI) and early predictors of POI during childhood. Furthermore, both genetic and epigenetic mechanisms underlying germ cell depletion will be investigated by integrating analyses of DNA methylation, gene expression, and proteomic profiles in ovarian and peripheral tissues.

## Methods

### Study design

This is a nation-wide, combined observational and interventional prospective cohort study with long-term follow-up. It is conducted across three university hospitals in Denmark and includes patients from all regions of the country. The study design is illustrated in Fig. 1. The study comprises four arms, defined by the initial assessment of the ovarian reserve and the remaining ovarian function following unilateral ovarian removal.

**Fig. 1 Fig1:**
[figure not shown]
Overview of the Danish Turner cryopreservation study: design and follow-up protocol. Abbreviations: TAUS = transabdominal ultrasound; DXA = dual-energy X-ray absorptiometry; HRpQCT = high-resolution peripheral quantitative computed tomography; QoL = quality of life

The trial protocol has been approved by the Scientific Ethics Committees for the Central Denmark Region (1-10-72-322-21). The study is registered at ClinicalTrials.gov (NCT05740579).

### Study period

Recruitment began in January 2024, and the study is expected to continue until 2050.

### Study population, inclusion and exclusion criteria

The study aims to include ovarian tissue for cryopreservation from a total of 100 girls with TS. Participants must be 2–17 years old with a confirmed diagnosis of TS, defined by a 45,X karyotype or a variant form such as 45,X/46,XX mosaicism, ring X mosaicism, or isochromosome X, in combination with typical clinical features of TS [21]. Exclusion criteria include severe cardiac disease contraindicating surgery and/or pregnancy, presence of Y chromosome material, and intellectual disability.

### Recruitment of participants and informed consent

Girls with TS and their parents will be informed about the study by their pediatric endocrinologist. Those who meet the inclusion criteria and express interest will receive detailed written information, tailored to the girl (if aged ≥ 15 years) and/or her parents. They will then be given as much time as needed to consider participation. Written informed consent must be obtained from all legal guardians. Girls aged ≥ 15 years must provide their own written consent in addition to that of their parents. Upon reaching the age of 18, participants will be asked to reconsent.

### Assessment of ovarian function

Since ovarian reserve is depleted before adulthood in most girls with TS, all participants undergo ovarian function assessment to evaluate the likelihood of remaining viable follicles. This approach aims to avoid unnecessary surgery and ensures that outcomes following OTC reflect the subgroup of girls with remaining viable follicles – and to whom OTC and later autotransplantation may be a feasible fertility preservation strategy.

Ovarian function is assessed through repeated measurements of serum hormone levels (including anti-Müllerian hormone (AMH), Inhibin B, gonadotropins (follicle stimulating hormone (FSH) and luteinizing hormone (LH)), and estradiol (E2)), clinical features of TS (such as pubertal development and current need for hormone replacement therapy), and imaging of the uterus and ovaries using transabdominal ultrasound (TAUS) and/or magnetic resonance imaging (MRI).

*Sufficient ovarian function for OTC was predefined as follows:*

In prepubertal girls: age-adjusted AMH >-2 SD or FSH < + 2 SD, along with antral follicle count (AFC) >10th percentile on TAUS or MRI [13, 22, 23].In peri-/postpubertal girls: spontaneous pubertal development >-2 SD according to puberty nomograms [24], AMH, E2, and inhibin B >-2 SD, FSH and LH < + 2 SD, along with AFC >10th percentile on TAUS or MRI [13, 22, 23].

*Insufficient ovarian function for OTC was predefined as follows:*

In prepubertal girls: AMH < -2 SD and FSH >+ 2 SD, along with streak ovaries or AFC < 10th percentile on TAUS or MRI [13, 22, 23].In peri-/postpubertal girls: absent or arrested pubertal development [24], primary or secondary amenorrhea, AMH, E2, and inhibin B < -2 SD, FSH >+ 2 SD, along with streak ovaries or AFC < 10th percentile on TAUS or MRI [13, 22, 23].

Following ovarian function assessment, the girls and their parents will discuss the results with both a gynecologist and a (pediatric or adult) endocrinologist with expertise in TS-related fertility. During this consultation, they will be informed about whether OTC can be offered, associated surgical risks, success rates of OTC in other patient groups, previous experiences with OTC in girls with TS, the risks associated with pregnancy, and alternative options for parenthood. They will also be informed about the increased risk of chromosomal abnormalities in potential children, and in the event of a pregnancy, the woman will be offered prenatal diagnostics (chorionic villus sampling). In cases where clinical, biochemical, and imaging findings do not provide a clear-cut assessment, cryopreservation may be considered following expert clinical assessment and a collaborative decision-making process with the family and the endocrinologist and/or gynecologist.

### Pre-operative assessment

According to the newly updated Clinical Practice Guidelines, recommendations against surgical intervention and/or pregnancy should be based on the patient’s individual cardiovascular risk profile [21]. Therefore, all participants deemed eligible for OTC will be examined by a trained cardiologist experienced in evaluating children and adolescents with TS. The examination includes transthoracic echocardiography (TTE), unless a recent examination is considered sufficient by the cardiologist. High-risk patients (and their parents) will be informed about the associated cardiovascular risks and will not be offered OTC if the risk of complications related to surgery or a future pregnancy is deemed too high.

### Additional baseline and follow-up assessments

In addition to blood samples and imaging performed for ovarian function assessment, a range of biological samples, imaging procedures, and clinical information is collected at baseline and at various follow-up intervals (Fig. 1). Buccal swabs are collected to screen for mosaicism using fluorescence in situ hybridization (FISH), as well as for DNA/RNA expression and methylation analyses. Additional blood samples are drawn for extended hormone profiling, assessment of bone turnover markers, and analyses of DNA/RNA expression and methylation. Bone health will be evaluated in all patients using dual-energy X-ray absorptiometry (DXA) to assess bone density and body composition. When practically feasible, high-resolution peripheral quantitative computed tomography (HRpQCT) will also be perfomed to examine bone microarchitecture. Free-living physical activity is tracked using a wearable activity monitor. Furthermore, quality of life is assessed using a questionnaire incorporating the WHO-5 Well-Being Index and the Satisfaction with Life Scale [25].

Examinations beyond standard care include DXA scans, HRpQCT (if offered), activity monitoring, buccal swab collection, MRI scan of the uterus and ovaries, and ovarian tissue cryopreservation (if offered). All procedures are provided free of charge, and participants (or their parents/legal guardians) will be reimbursed for travel expenses.

### Ovarian tissue cryopreservation (OTC)

The ovary is removed by laparoscopic unilateral oophorectomy, performed either at Copenhagen University Hospital – Rigshospitalet or at Aarhus University Hospital. The procedure is carried out by pediatric surgeons or gynecologists, depending on the patient’s age and maturity level. Ovaries removed at Aarhus University Hospital are placed in a specialized transport medium (Custodiol-HTK, Koehler-Chemie, Germany) and cooled during transfer (4–5 hours) to the Laboratory of Reproductive Biology at Copenhagen University Hospital – Rigshospitalet, where the tissue is processed and cryopreserved [26]. If the ovary is removed locally, it is transported in McCoy’s 5a medium with 25 mM HEPES at 37 °C to the same laboratory. Before cryopreservation, small biopsies (1–4 mm) are taken from both the ovarian cortex and medulla for analysis of follicle density, level of mosaicism, and assessment of DNA methylation status and RNA expression. If small antral follicles are present in the ovaries, follicular fluids with granulosa cells and immature oocytes will be aspirated and collected. In vitro maturation of collected immature oocytes will be attempted according to a previously developed protocol [27]. If surplus medullary tissue is available, enzymatic isolation and culture of preantral follicles will be attempted according to standard protocols [28].

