### Statistical analysis

Statistical analyses will be performed using STATA and SPSS. Methylation and RNA expression analyses will be conducted using R (EdgeR, DESeq2, Minfi).

Descriptive statistics will be used to analyze the number of ongoing pregnancies, miscarriages, and live births following autotransplantation of cryopreserved and thawed ovarian tissue, as well as the number of primordial follicles, time to pregnancy, and time to live birth. Continuous variables will be summarized as means with standard deviations (SD) or medians with interquartile ranges (IQR), depending on data distribution. Categorical variables will be summarized as percentages.

Associations will be assessed using Spearman’s correlation coefficient, including relationships between age at cryopreservation, hormone levels, and the number of primordial follicles.

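### Ovary transport differs completely by operating hospital, and the plain Spearman correlation named for follicle associations cannot allow for it

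*Protocol article*

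**What the plan says.** Under Ovarian tissue cryopreservation (OTC), the oophorectomy is "performed either at Copenhagen University Hospital – Rigshospitalet or at Aarhus University Hospital". Aarhus ovaries go into Custodiol-HTK and are "cooled during transfer (4–5 hours) to the Laboratory of Reproductive Biology" in Copenhagen. For the other route the text reads: "If the ovary is removed locally, it is transported in McCoy’s 5a medium with 25 mM HEPES at 37 °C to the same laboratory". No duration is given for that route.

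The same section continues: "Before cryopreservation, small biopsies (1–4 mm) are taken from both the ovarian cortex and medulla". These samples serve to measure follicles, mosaicism, methylation and RNA. Small antral follicles are aspirated and in vitro maturation is attempted on the oocytes. The section places tissue processing at the Copenhagen laboratory.

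Secondary outcomes include primordial follicle density in relation to karyotype, age, hormonal status and imaging, and the association of methylation and RNA expression with POI in leukocytes and ovarian tissue.

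The Statistical analysis section says: "Associations will be assessed using Spearman’s correlation coefficient", and gives age at cryopreservation, hormone levels and primordial follicle number as examples. For methylation and RNA expression it names R packages (edgeR, DESeq2, Minfi) and no model terms. The article does not mention operating hospital, transport medium, temperature or transport time as a covariate, stratum or batch term.

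**The concern.** Medium and temperature are decided entirely by which hospital operates. Handling and hospital are therefore the same two-level variable, and every ovary carries one level or the other before its tissue is sampled.

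Two consequences are possible for any tissue measure that is sensitive to handling. If the predictor (age, AMH, FSH and so on) has the same distribution at both hospitals, the handling shift only widens the scatter and weakens real correlations. If the predictor also differs between hospitals, the two shifts line up and create, inflate or mask a correlation. A rank correlation pooled over both hospitals cannot tell that from biology. The follicle-density associations matter because the study intends to use such findings to refine selection for OTC.

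**Working it through.** **Inputs from the protocol article.** Two operating hospitals; two media and two temperatures, one pair per hospital; a target of 100 girls undergoing OTC; Spearman correlation as the named method. The one computed figure in the article, the sample size of 72, reproduces (4 × 1.96² × 0.25 × 0.75 / 0.2² = 72.03) but has no bearing on this point.

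**Inputs that the article does not give, so assumed.** Share of ovaries from Aarhus, p = 30% or 50%. Handling shift in the tissue measure, d_y = 0.5 or 1 SD. Difference in the predictor between hospitals, d_x = 0, 0.5 or 1 SD.

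**Formula.** With no true association within hospitals, pooling induces a correlation of about

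r = p(1−p)·d_x·d_y / √[(1 + p(1−p)d_x²)(1 + p(1−p)d_y²)].

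Example with p = 0.5, d_x = 0.5, d_y = 1: 0.25 × 0.5 / √(1.0625 × 1.25) = 0.125 / 1.152 = 0.108. With n = 100, z ≈ 0.108 × √99 ≈ 1.08. The chance of |z| > 1.96 is then about 0.19 instead of 0.05.

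**Simulation with the named method.** n = 100, 6,000 runs per row, no true association, two-sided 5% test. The adjusted version is a partial rank correlation with hospital removed from both sets of ranks. Monte Carlo standard error near 5% is √(0.05 × 0.95 / 6000) = 0.3 percentage points.

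| Aarhus share | d_x | d_y | r from formula | Plain Spearman, false positives | Hospital-adjusted |
|---|---|---|---|---|---|
| 30% | 0 | 0.5 | 0 | 4.8% | 4.8% |
| 30% | 0 | 1 | 0 | 5.2% | 5.2% |
| 30% | 0.5 | 0.5 | 0.050 | 8.1% | 4.8% |
| 30% | 0.5 | 1 | 0.093 | 14.7% | 5.0% |
| 30% | 1 | 0.5 | 0.093 | 14.5% | 5.2% |
| 30% | 1 | 1 | 0.174 | 39.5% | 5.9% |
| 50% | 0 | 0.5 | 0 | 4.9% | 5.0% |
| 50% | 0 | 1 | 0 | 4.9% | 4.5% |
| 50% | 0.5 | 0.5 | 0.059 | 8.5% | 5.2% |
| 50% | 0.5 | 1 | 0.108 | 19.0% | 5.0% |
| 50% | 1 | 0.5 | 0.108 | 18.6% | 4.7% |
| 50% | 1 | 1 | 0.200 | 53.1% | 5.1% |

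**Noise only.** With a true within-hospital correlation of 0.3 and a balanced predictor (d_x = 0), power of plain Spearman is 81% for d_y = 0.5 (either share), and 74% (30% share) or 73% (50% share) for d_y = 1. Adjusted for hospital it is 82–83% throughout.

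**What this shows.** Bias needs both shifts. With one of them absent the error rate is intact and the loss is modest power. With both present, adjustment brings the error rate back to about 5–6%.

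**The case against.** The strongest objection is that most of this is silence rather than error. A condensed article need not list design-matrix terms, and an analysis plan that is not shown may already hold a hospital or batch term for the expression and methylation models. That is right, and the point does not claim that those models are wrong. The one-sentence Spearman statement could also be shorthand for a stratified or partial version. That is possible, but the coefficient as named has no place for a covariate, and the handling difference is created by the protocol itself.

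Second, nothing in the documents shows that transport alters any tissue measure or that case mix differs by hospital. Recruitment is nationwide, the eligibility definitions are common, and all ovaries are processed in one laboratory. This also stands. It is why the figures are conditional, and why a balanced predictor leaves the false-positive rate near 5%.

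Several stronger readings are tempting and are not supported:

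- A reader might infer that every ovarian tissue measure is distorted. No effect is documented for any of them, and for some, such as level of mosaicism, the documents give no reason to expect one.
- A reader might infer that transport times are known to differ. The local time is not stated; a shorter one is plausible but inferred.
- A reader might treat sampling after transport as stated fact. It is the natural reading of a section that puts processing at the laboratory, not an explicit statement.
- A reader might extend the point to pregnancies and live births after autotransplantation. The working does not cover those outcomes, and the plan analyses them descriptively.
- A reader might infer that one transport procedure is wrong. Nothing here bears on that.

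**Conclusion.** The point holds in a limited form. Handling is completely aliased with operating hospital for ovarian tissue, and plain Spearman correlation, the only association method named, cannot account for it. The harm is possible, not shown: noise if handling affects the measure, and bias only if the predictor also differs between hospitals. Under assumed shifts of 0.5 SD each, or 0.5 SD in one and 1 SD in the other, the false-positive rate with 100 ovaries is about 8–19%. It reaches 40–53% only if both shifts are a full SD, and it stays near 5% if the predictor is balanced. These are sensitivity figures and do not estimate the error in this study. Blood and buccal measures are unaffected. The affected outcomes are secondary in a study that calls itself exploratory, so this is an inexpensive improvement to the analysis and not a flaw in the primary result.

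**What to change.** 1. For follicle density and number, replace plain Spearman with a partial rank correlation adjusted for operating hospital, or a hospital-stratified rank correlation.
2. If the analysis plan does not already do so, include operating hospital/transport route as a term in the edgeR, DESeq2 and Minfi models of ovarian tissue, and only of ovarian tissue.
3. If it is not already recorded, record the time from excision to laboratory processing for every ovary. Recruitment began in January 2024, so for girls already operated on it may be hard to recover later.

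The cost is wording in the analysis plan, one recorded time per ovary, and about one degree of freedom per model (97 instead of 98 for a correlation on 100 ovaries). Hospital should already be known for each girl. The limitation to state is that the term removes the combined hospital-and-handling shift but cannot separate transport from other differences between the hospitals. No change to either transport procedure is proposed.

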### Ovarian tissue autotransplantation

Prior to pregnancy planning, fertility potential will be evaluated by a gynecologist or fertility specialist to assess the likelihood of spontaneous conception or indication for assisted reproductive technology (ART) and/or autotransplantation. If autotransplantation is indicated, preoperative screening is performed according to current guidelines. The procedure is carried out using minimally invasive surgery (laparoscopy or mini-laparotomy), where thawed ovarian tissue is transplanted into the remaining ovary or, if feasible, into peritoneal pockets. Follow-up includes hormonal assessment and transvaginal ultrasound to assess tissue activity. Further fertility planning will depend on signs of graft function and the patient will be treated according to a standard ART protocol.

